## Abstract

**Background:**

More than 950,000 adults over 65 years of age are hospitalized each year after injury. Recommended care for this vulnerable group includes discussion of their goals for life-sustaining care (“code status”) upon admission, but most older patients do not participate in adequate code status discussions. Randomized trials have demonstrated that video-based interventions are associated with better patient knowledge and improved alignment of patient preferences for life-sustaining treatment; however, there are limited data on the effectiveness of these interventions in acutely injured patients.

**Objective:**

This trial will evaluate the effectiveness and implementation considerations of a video conversation aid to enhance communication among trauma care providers, patients, and surrogate decision-makers regarding cardiopulmonary resuscitation (CPR) and code status decisions.

**Methods:**

This is a single-center randomized controlled trial evaluating the use of a video conversation aid to facilitate discussions of code status. The video intervention will be compared to usual care in the largest feasible pilot randomized controlled trial with the goal of estimating its benefit for patient-centered outcomes. All trauma patients aged 65 years and older admitted following injury are eligible. Incarcerated people, patients with existing do-not-resuscitate or do-not-intubate orders, patients admitted while in hospice care, and patients not expected to survive over 24 to 48 hours will be excluded. The primary outcome is transitions in code status. Secondary outcomes will include perceived success of CPR, video acceptability and effectiveness, knowledge of life-sustaining care outcomes and complications following CPR, participant desire for more information regarding life-sustaining care, hospital-free days, intensive care unit–free days, ventilator-free days, discharge disposition, decisional conflict score, and rate of interventional procedures (eg, tracheostomy, feeding tube placement, and dialysis initiation).

**Results:**

The ADVISE (Advancing Discussions Using a Video-Based Support Tool About End-of-Life Care) trial was funded in February 2025 via the Learning Healthcare System grant from the University of Texas Health Science Center at Houston. Enrollment began on March 17, 2025, and it is estimated to conclude on May 1, 2026.

**Conclusions:**

The ADVISE trial builds on previous research on older trauma patients and advanced care planning using a video intervention to enhance code status discussions. We anticipate that our video aid tool will enhance patients’ and surrogate decision-makers’ knowledge of advanced care discussions.

**Trial Registration:**

ClinicalTrials.gov NCT06804226; https://clinicaltrials.gov/study/NCT06804226

**International Registered Report Identifier (IRRID):**

DERR1-10.2196/87690

## Introduction

Traumatic injury is responsible for more than 950,000 hospitalizations in adults over 65 years of age each year [1]. The American College of Surgeons Best Practices Guidelines advise that care for this vulnerable group should include a discussion regarding goals for life-sustaining care (sometimes referred to as “code status”) upon admission [2]. However, there are multiple barriers to having effective code status discussions with older injured patients, and most injured older adults do not receive this counseling [3]. Randomized trials have demonstrated that video-based interventions are associated with deeper patient understanding and patient choices that avoid acute cardiopulmonary resuscitation (CPR) [4]. There are limited data on the effectiveness of video-based interventions in the acutely injured population.

One identified barrier is the lack of understanding on the part of many patients of the associated risks and benefits of CPR and preconceived unrealistic expectations of its success [5,6]. As one of the largest physician barriers to engaging in code status discussions is time constraints, this lack of knowledge regarding CPR is often never addressed [7-9]. When discussions do occur, physicians often use medical jargon and infrequently provide prognostic information [7]. As a result, code status discussions are often brief and ineffective at communicating and increasing understanding of life-sustaining interventions, limiting the ability of patients and surrogate decision-makers to make informed decisions about critical care goals [8-10].

This multidisciplinary, collaborative research project will evaluate the effectiveness of a video aid to improve communication and patient-centered outcomes in older injured adults. This video conversation aid is not intended to replace code status discussions between patients and health care providers but to promote these discussions. The goal is to overcome identified barriers to adequate code status discussions by providing a clear message with no medical jargon; supplying accurate prognostic information; and, ultimately, enhancing informed consent so that patients can ensure that their care choices align with their preferences. We hypothesize that our video aid will increase the rate of code status transitions, with more patients documenting their code status. Additionally, we hypothesize that our video aid will improve knowledge of life-sustaining care and increase code status discussions.

## Methods

The trial was designed in accordance with the SPIRIT (Standard Protocol Items: Recommendations for Interventional Trials) 2013 guidelines [11].

### Study Setting

Our trial will be conducted at the Red Duke Trauma Institute at Memorial Hermann–Texas Medical Center. This center is 1 of only 2 adult level 1 trauma centers in the city of Houston, Texas, and serves over 7 million people. Approximately 200 trauma patients aged ≥65 years are admitted per month, leading to over 2800 total older adult inpatients per year.

### Study Population

All English- or Spanish-speaking patients aged 65 years or older admitted to any level of care following traumatic injury will be screened for study eligibility. As this is a pilot trial, we will have minimal exclusion criteria except for (1) incarcerated people, (2) existing do-not-resuscitate (DNR) or do-not-intubate (DNI) orders, (3) patients admitted while in hospice care, and (4) patients not expected to survive over 24 to 48 hours. Incarcerated individuals are excluded due to being a vulnerable population in a study that waives informed consent. Patients with established DNR or DNI orders have already made decisions regarding their code status; therefore, including them would impede our ability to assess the intervention’s effect on code status decision-making. Auditory and visual impairments are not barriers to participation. The code status video includes subtitles, and patients have the option to have the research assistant administer the study survey verbally. All patients who meet the eligibility criteria will be offered enrollment within 48 hours whenever feasible.

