### Procedures and Outcomes

A research assistant will administer a survey to each participant at discharge either collected verbally or completed electronically via QuestionPro. Patients’ decision-making capacity is determined by the primary clinical team. For patients who die during admission, surrogate decision-makers will be contacted after discharge. Demographics, injury characteristics, length of stay, preexisting advanced directives, and disposition will be collected using the institutional trauma registry. Each participant will be assigned a study-specific number.

The primary outcome will be the rate of transition in code status. Prior institutional data have shown that a minority of patients have advanced directives or code status discussions with their providers; therefore, this serves as a proxy for increased patient or surrogate decision-maker knowledge.

Secondary outcomes will include perceived success of CPR, knowledge of life-sustaining care outcomes and complications following CPR, and participant desire for more information regarding life-sustaining care. These will all be assessed using a Likert scale via a survey at the time of discharge. Decisional conflict score will also be assessed at the time of discharge using an electronic survey. Hospital-free days, intensive care unit (ICU)–free days, ventilator-free days, discharge disposition, and rate of interventional procedures (eg, tracheostomy, feeding tube placement, and dialysis initiation) will be collected from the electronic medical record.

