### Data Analysis Plan

Analysis will be performed on a per-patient basis. For patients who are incapacitated and unable to consent for themselves, their surrogate decision-makers will serve as the participant for analysis. The number of screened patients and reasons for exclusion will be reported. Protocol violations and reasons for those violations will be reported and detailed. All analyses will be based on the intention-to-treat principle. Regarding the primary end point, we will estimate the risk ratio between the intervention and usual care groups together with a 95% Wald CI. For other outcome variables, we will implement 2-group comparisons using the Wald test for dichotomous variables and the Wilcoxon rank-sum test for continuous variables. ICU-free days and ventilator-free days refer to the number of days during admission without intensive care or a ventilator [15]. In case of a death event, these variables are set to a value of 0. The principal investigator will audit data collection to ensure that the data are accurate, consistent, complete, and reliable.

For the primary end point, in addition to the frequentist inference, we will conduct a Bayesian analysis to enhance the knowledge gained from the study. Bayesian analysis enhances the clinical decision-making process by integrating existing evidence with data from a new study to estimate the probability of an outcome of interest. In contrast, frequentist analysis assesses the likelihood of observing the obtained results or more extreme outcomes. For each group, we will use the conjugate β prior for the probability of transition in code status. The parameter values for β distribution will be chosen to center a symmetrical distribution at 0.5, and the corresponding distribution for the risk ratio will be centered at 1 with a credible interval of 0.5 to 2.0, resulting in a neutral prior [16]. Additionally, we will perform sensitivity analysis by identifying suitable β prior distributions to generate enthusiastic and skeptical priors. We will use the JAGS software (version 4.3.2) for Bayesian analysis. All other statistical analyses will be performed using the SAS software (version 9.4; SAS Institute).

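### The exclusion for prior code status decisions tests for an order, so patients whose existing directive already declines CPR or intubation are eligible, and the planned analysis does not separate them

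*Protocol article*

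**What the plan says.** The protocol article, Study Population, lists four exclusions. One concerns incarceration. Two concern hospice care and expected early death: "3) patients admitted while in hospice care, and (4) patients not expected to survive over 24 to 48 hours". Only one concerns a code status choice already made: "2) existing do-not-resuscitate (DNR) or do-not-intubate (DNI) orders". The reason given is that "Patients with established DNR or DNI orders have already made decisions regarding their code status" and that "including them would impede our ability to assess the intervention’s effect on code status decision-making". Advance directives are not mentioned there.

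The article does foresee patients with directives. Procedures and Outcomes states: "Demographics, injury characteristics, length of stay, preexisting advanced directives, and disposition will be collected using the institutional trauma registry". That section and the Discussion both expect directives in a minority of patients and give no number.

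The primary outcome is the code status transition rate. After noting how few patients have directives or discussions, the article says: "therefore, this serves as a proxy for increased patient or surrogate decision-maker knowledge". The Limitations section adds that an active choice of full code is neither tracked nor reflected in the outcome.

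For the primary analysis, Data Analysis Plan says "we will estimate the risk ratio between the intervention and usual care groups together with a 95% Wald CI", on the intention-to-treat principle, with a Bayesian analysis using a beta prior for each arm. The planned stratification factor is patient versus surrogate viewer. The listed subgroups are race, gender, health literacy, and patient versus surrogate. Directive status appears in none of these places.

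**The concern.** The stated reason for the exclusion is a prior decision, but the criterion detects only an order. A patient with a living will that refuses CPR, and no inpatient order at screening, fits the reason and passes all four exclusions. If the team later learns of the directive and writes the order, the chart shows a move away from full code. The Limitations section suggests that this is the kind of event being counted.

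No new decision was made and no knowledge was necessarily gained. The primary endpoint then mixes two kinds of event: decisions made after new information, and earlier decisions now entered as orders. The reported risk ratio and probability of benefit cannot tell the reader which kind drove the result. The article already collects a variable that could help separate them, but the stated analysis does not use it.

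**Working it through.** **Inputs from the article.** Enrollment of 15 per month for 18 months gives 15 × 18 = 270, which reproduces the stated sample size; 1:1 allocation gives 135 per arm. The article states no event rate, effect size, power or directive prevalence.

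**Assumptions (illustration only).** Let f be the share of patients holding a directive that declines CPR or intubation, and q their transition rate. Patients without one transition at 10% under usual care and 20% with the video, a risk ratio (RR) of 2.0.

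**Case 1: directive holders transition equally in both arms.**
- Usual care rate = (1 − f) × 0.10 + f × q
- Video rate = (1 − f) × 0.20 + f × q

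| f | q | Usual care | Video | RR | Holders' share of usual-care transitions |
|---|---|---|---|---|---|
| 5% | 10% | 0.100 | 0.195 | 1.95 | 5% |
| 5% | 80% | 0.135 | 0.230 | 1.70 | 30% |
| 10% | 50% | 0.140 | 0.230 | 1.64 | 36% |
| 20% | 30% | 0.140 | 0.220 | 1.57 | 43% |
| 30% | 80% | 0.310 | 0.380 | 1.23 | 77% |

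At f = 10% and q = 50%, power (two-sided 0.05, normal approximation) is 0.48 with holders included (270 patients) and 0.59 without them (243 patients). The smaller set is more informative here because the excluded patients add events but no contrast.

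**Case 2: the video only prompts existing directives to be written as orders.** Holders transition at 30% versus 60%; everyone else transitions at 10% in both arms.
- f = 5%: 0.110 versus 0.125, RR 1.14
- f = 10%: 0.120 versus 0.150, RR 1.25
- f = 20%: 0.140 versus 0.200, RR 1.43
- f = 30%: 0.160 versus 0.250, RR 1.56

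Here the trial would show a benefit with no new decision made.

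**Chance imbalance.** The SD of the between-arm difference in prevalence is √(2f(1 − f)/135), or 2.65 percentage points at f = 5% and 5.58 at f = 30%. At f = 20% it is 4.87 points, so the 95% range is 1.96 × 4.87 = ±9.5 points. With a 20-point gap in transition rate between holders and others, that moves the arm difference by up to 0.095 × 0.20 = 1.9 points. The 95% half-width of the risk difference at 14% versus 22% is 1.96 × √((0.14 × 0.86 + 0.22 × 0.78)/135) = 9.1 points, so imbalance is a small part of the ordinary sampling error.

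**What adjustment does and does not do.** With directives balanced across arms, a Mantel-Haenszel RR at f = 20%, q = 30% is (0.2 × 0.30 + 0.8 × 0.20)/(0.2 × 0.30 + 0.8 × 0.10) = 0.22/0.14 = 1.57, the same as the crude value. Adjustment handles chance imbalance. Only results by directive status, or without the holders, separate the two kinds of event.

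**The case against.** The strongest reply has four parts.

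- **Broad eligibility is deliberate.** The article presents minimal exclusions as a feature of a pilot trial. A directive without an order leaves the inpatient code status unsettled, which is the gap the trial addresses. The hypothesis also predicts more documentation of code status, so an order prompted by an earlier directive may be an intended effect. This stands in part: counting such events is not plainly an error. But documentation and knowledge gain are different claims, and the article makes the outcome a proxy for knowledge.
- **The inference goes beyond the text.** A reader might infer that these patients are entered as full code and that their later orders necessarily count as primary events. The documents do not say so. The article defines neither the baseline state nor the qualifying event, and the full protocol or SAP may. What stands is narrower: nothing shown prevents it.
- **The direction is not known.** A reader might infer that such orders must pull the result toward no effect, or that they confound the comparison. The first follows only if holders transition equally in both arms, and Case 2 goes the other way. The second is ruled out by 1:1 randomization with intention-to-treat analysis. The overall RR remains a valid effect in the enrolled population, and chance imbalance is already within the Wald interval.
- **Adjustment and sensitivity sets belong in a SAP.** This is fair, and their absence from an article is not itself a fault. The point rests on the mismatch between the exclusion and its stated reason, which the article fixes, and on an endpoint interpretation that the stated unadjusted analysis cannot test.

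**Conclusion.** The point holds in a limited form. Among the criteria about prior code status decisions, the article excludes only patients with orders, although its reason applies equally to patients whose directive already declines CPR or intubation. An order that later carries out such a directive may count as a transition, and that event would not show the knowledge gain attributed to the outcome.

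The consequence is dilution or a changed meaning of the endpoint. It does not invalidate the randomized comparison. Under the assumed rates, and for prevalence of 5% to 30%, an RR of 2.0 shrinks to between 1.95 and 1.23 if holders behave alike in both arms. If the video acts only through existing directives, the RR is 1.14 to 1.56. The true size and direction cannot be determined from the article: prevalence is described only as a minority, the content of directives is not given, and every rate used here is an assumption. The point is worth acting on mainly because the remedy is cheap and still available.

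**What to change.** Amend Data Analysis Plan before anyone sees unblinded results; the article plans an abstract by July 2026.

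1. Keep all randomized patients in the intention-to-treat primary analysis, and estimate the primary risk ratio stratified by, or adjusted for, preexisting advance directive at admission (yes/no).
2. Report transitions in each arm by directive status.
3. Repeat the frequentist and Bayesian primary analyses without patients whose directive predates admission.

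Directive status at admission precedes randomization, so none of these steps breaks the randomized comparison.

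The cost is a few lines of text and a modest amount of data work. The sensitivity set is smaller (243 of 270 if 10% hold a directive). Directives must be dated so that only those made before admission count. The registry may record only that a directive exists; whether it declines CPR or intubation may then need chart abstraction. Without that, step 3 also removes patients whose directive says nothing about either.

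Changing the exclusion criterion is not proposed: the Results section reports that the planned 270 patients were enrolled as of April 2026.

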### Intervention Group

A video conversation aid that provides information about life-sustaining care and encourages further discussions on goals of care with a health care provider will be shown to patients or their surrogate decision-makers upon admission or within 48 hours, whichever is more feasible. The video aid is available in both English and Spanish. Surrogate decision-makers are required for patients who lack decision-making capacity, specifically, those unable to understand their medical condition, appreciate the consequences of treatment options, or engage in rational decision-making [2]. This video will be administered by a research assistant who is not part of the patient’s care team.

The video script was created by a multidisciplinary team encompassing emergency medicine, palliative care, geriatric medicine, internal medicine, and trauma surgery along with content experts in health literacy and medical ethics. An iterative approach was used, and script development followed the International Patient Decision Aids Standards Collaboration quality criteria as a framework for the creation of the video decision aid. The goal of the video was to provide standardized information for code status discussions. After providers reached consensus, the script was revised based on feedback from community patient representatives and patients from a standardized patient advocacy group at MD Anderson Cancer Center. Adjustments were made to simplify the medical language and better accommodate patients with low health literacy. The final video was produced by the Kashu animation company at a fourth-grade reading level in both English and Spanish. An animated format was chosen based on feedback from community groups indicating that it was the least distressing to patients. After the animated video was created, it was reassessed by the community group for final feedback and found to be both easy to follow and not distressing to patients. After administration of the code status video, if patients choose to change their code status or have additional questions, they may discuss them with their primary inpatient medical care team. For patients who experience distress, additional support is available through the supportive medicine team and chaplaincy services.

### Usual Care Group

Patients and/or surrogate decision-makers will participate in discussions surrounding life-sustaining care at health care providers’ discretion. This task is most often completed by resident physicians, but there is no standardization regarding participants or timing.

### Procedures and Outcomes

A research assistant will administer a survey to each participant at discharge either collected verbally or completed electronically via QuestionPro. Patients’ decision-making capacity is determined by the primary clinical team. For patients who die during admission, surrogate decision-makers will be contacted after discharge. Demographics, injury characteristics, length of stay, preexisting advanced directives, and disposition will be collected using the institutional trauma registry. Each participant will be assigned a study-specific number.

The primary outcome will be the rate of transition in code status. Prior institutional data have shown that a minority of patients have advanced directives or code status discussions with their providers; therefore, this serves as a proxy for increased patient or surrogate decision-maker knowledge.

Secondary outcomes will include perceived success of CPR, knowledge of life-sustaining care outcomes and complications following CPR, and participant desire for more information regarding life-sustaining care. These will all be assessed using a Likert scale via a survey at the time of discharge. Decisional conflict score will also be assessed at the time of discharge using an electronic survey. Hospital-free days, intensive care unit (ICU)–free days, ventilator-free days, discharge disposition, and rate of interventional procedures (eg, tracheostomy, feeding tube placement, and dialysis initiation) will be collected from the electronic medical record.

